## Version 2.6

$\mu_{pH}$ ;  $0.38 - 0.17 = 0.21$ ) after 12 weeks of administration of 5 mg pilocarpine and placebo was set as the non-inferiority limit.

- Reference: Vivino FB, et al. Pilocarpine tablets for the treatment of dry mouth and dry eye symptoms in patients with Sjögren syndrome: a randomized, placebo-controlled, fixed-dose, multicenter trial. P92-01 Study Group. Arch Intern Med. 1999. PMID: 9927101 Clinical Trial.
- The H01 and H11 of this clinical trial are as follows.

H01:  $\mu_c - \mu_t > 0.21$

H11:  $\mu_c - \mu_t \leq 0.21$

$\mu_c$  = SFR after 12 weeks of administration of only pilocarpine one tablet

$\mu_t$  = SFR after 12 weeks of combined administration of Baekhogainsam-tang herbal medicine and low-dose pilocarpine

$$n_c = \frac{(1 + \lambda) \sigma^2 (Z_{\alpha} + Z_{\beta})^2}{\lambda (|\mu_c - \mu_t| - d)^2}$$

$N_c = N_t = 48$

- Assuming a 20% dropout rate, we calculated the sample size as 120 participants (60 in each group).

|                                     | Control | Experimental | Total |
|-------------------------------------|---------|--------------|-------|
| Resultant sample size               | 48      | 48           | 96    |
| Sample size considering 20% dropout | 60      | 60           | 120   |

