#### **4.2.2. Backgrounds for conventional treatments**

- The treatment of intractable xerostomia requires addressing systemic diseases, adjusting medications and modifying lifestyle factors. Local spray medications, sugar-free gums, adequate hydration, and lubricants are commonly employed. Local spray drugs can be divided into saliva gland secretion stimulants including gum and candy, and saliva alternatives. Saliva gland secretion stimulants include stimulants including malic acid, sugar-free gum, mouth rinse, gels, and toothpaste, which stimulate saliva secretion. Saliva substitute contains olive oil, betaine, glycerol, etc., similar to natural saliva and acts by increasing the salivary viscosity.
- However, these treatments have certain limitations in patients who have received radiotherapy for head and neck cancer or with Sjogren's syndrome, which are the main causes of intractable xerostomia. Pilocarpine has been approved by the US Food and Drug Administration (FDA) to increase salivary secretion in these patients. However, its efficacy diminishes when a significant portion of the glands is damaged. It often exhibits more side effects at high-doses and limited effectiveness at low-doses. Prolonged high-dose

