## Version 2.6

vomiting, diarrhea, atrioventricular block, tachycardia, bradycardia, hypotension, hypertension, shock, delirium, arrhythmia, and progression. However, there are no other drugs available to patients with xerostomia in actual clinical practice due to pilocarpine' side effects.

- In this study, we want to confirm the effect of administrating both pilocarpine at half dose of commercial dose (previous clinical trial reported that half dose of pilocarpine was significantly less effective than the commercial dose) and Baekhogainsam-Tang (increasing salivary gland secretion, and improving the salivary gland secretion of pilocarpine) compared to administrating only pilocarpine at commercial dose. In other words, the design basis and goal of this study is to verify that the co-administration of Baekhogainsam-Tang has the same efficacy and reduced side effects while reducing the administration of pilocarpine.
- The paper on the basis of co-administration  
Pilocarpine, a muscarinic agonist, significantly increases salivary gland secretion, but its action is inhibited by anticholinergic drugs such as oxybutynin and propionate. In animal experiments, the salivary glands' stimulation of pilocarpine inhibited by oxybutynin was significantly recovered when BIT was co-administered.

[figure not shown]

Fig. 4. Effect of BN on salivary secretions (1–3 h) in anesthetized rats treated with oxybutynin and pilocarpine. BN was administered p.o. just before administration of oxybutynin. After 10 min, pilocarpine was injected i.p. Each column and vertical bar represents the mean  $\pm$  S.E. of six animals. \* $P$  < 0.05 and \*\* $P$  < 0.01 compared to oxybutynin (10 mg/kg, p.o.) + pilocarpine-treated group (8 mg/kg, i.p.).

( Masaru S., Kazuhiro G., Hiroyuki I.,

Version 2.6

et al. Effects of Byakko-ka-ninjin-to on salivary secretion and bladder function in rats. J  
Ethnopharmacol. 2005 Nov 14;102(2):164-9.)

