#### 8.4. Basis for sample size calculation

- The aim of this prospective, randomized, open-label, parallel-group, multi-center, and controlled trial is to ascertain whether combined administration of BIT herbal medicine and low-dose pilocarpine can demonstrate both non-inferior efficacy and fewer side effects in patients with frequent intractable xerostomia (patients who underwent radiation therapy to the head and neck or with Sjogren's syndrome) than the administration of only high-dose pilocarpine.
- The assumptions for calculating the valid sample size are as follows.
  - ① One-sided Z test (Non-inferiority test)
  - ② Level of significance ( $\alpha$ ) = 0.05 (Considering this is an intervention study)
  - ③ Type 2 error ( $\beta$ ) = 0.1 (Power of the test = 90%)
  - ④ Experimental group: Control group = 1 : 1 ( $\lambda=1$ )
  - ⑤ Primary outcome: unstimulated salivary flow rate (SFR) after 12 weeks of treatment
- $\sigma = 0.35$  / d (non-inferiority limit) = 0.21

In the previous study, the mean  $\pm$  standard deviation (SD) of unstimulated SFR for 5 mg pilocarpine therapy vs placebo group after 12 weeks of medication, respectively, were  $0.38 \pm 0.48$  vs  $0.17 \pm 0.13$  mL/min ( $p < 0.001$ ). Based on these results, the SD was calculated to be 0.35.

In consideration of the exploratory aspects of the clinical trial, the point estimation ( $\mu_{CIH}$  -

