#### **13.3.1.2. Statistical methods**

- A 95% confidence interval (95% CI) will be used to analyze primary outcomes.
- We will calculate the 95% CI of the mean difference in the unstimulated SFR between the two groups after 12 weeks of medication. If the lower end of the 95% CI of the mean difference is greater than the non-inferiority limit ( $-0.21$ ), it will be concluded that the experimental group is not inferior to the control group.
- For further analysis, if the SFR between the two groups satisfy the normality test, a t-test will be performed to compare the two groups in terms of the primary outcomes; otherwise, the Mann-Whitney U test will be performed. If there is a significant difference in baseline values between the two groups, repeated-measures analysis of covariance (ANCOVA) will be performed.

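### The non-inferiority limit of 0.21 mL/min is the entire historical pilocarpine-versus-placebo difference, so meeting it does not support an unqualified conclusion of non-inferiority

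*Protocol*

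**What the plan says.** Section 8.4 of the protocol, repeated in the synopsis, sets "d (non-inferiority limit) = 0.21" mL/min. The figure is the difference in week-12 unstimulated salivary flow between 5 mg pilocarpine and placebo in one cited trial in Sjögren's syndrome: "0.38 - 0.17 = 0.21". The point estimate "after 12 weeks of administration of 5 mg pilocarpine and placebo was set as the non-inferiority limit". The only reason offered is "In consideration of the exploratory aspects of the clinical trial". From the same trial (SDs 0.48 and 0.13) "the SD was calculated to be 0.35", which leads to 48 evaluable participants per group and 60 after a 20% dropout allowance.

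Section 13.3.1.2 and the statistical methods in the synopsis give the decision rule. If the lower end of the 95% CI for the difference lies above -0.21, "it will be concluded that the experimental group is not inferior to the control group". No qualification is attached. Section 4.1 states the efficacy objective as non-inferiority, and section 4.5 describes the goal as equal efficacy at a reduced pilocarpine dose. Section 4.5 also notes that an earlier trial found that "half dose of pilocarpine was significantly less effective than the commercial dose".

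**The concern.** A non-inferiority limit says how much of the control treatment's benefit the new regimen may lose and still be called not inferior. Here the permitted loss is all of it. The limit is the full historical effect, taken at its point estimate. It is neither a fraction of that effect nor its lower confidence limit, and no clinical argument supports its size.

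Two things follow. First, excluding a deficit of 0.21 is compatible with a material loss of efficacy, so the word attached to success says more than the result can show. Second, the historical estimate has its own error. If pilocarpine's true advantage over placebo in this trial's population is below 0.21, an arm no better than placebo lies inside the limit and can be declared not inferior. The primary conclusion of the trial is at stake. An analysis plan cannot easily repair it, because the protocol fixes both the limit and the sentence that follows from meeting it.

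**Working it through.** **Inputs.** From section 8.4: limit 0.21; historical means 0.38 and 0.17; SDs 0.48 and 0.13; p < 0.001; SD for sizing 0.35; one-sided α 0.05; power 90%; 1:1 allocation; dropout 20%. From 13.3.1.2: lower 95% CI limit above -0.21. I read that interval as two-sided and use 48 evaluable per arm, because the per-protocol set is the main analysis (13.1.3).

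**The plan's own figures reproduce.**
- SD: √((0.48² + 0.13²)/2) = 0.352, rounded to 0.35.
- n per group: 2 × 0.35² × (1.645 + 1.282)² / 0.21² = 47.6, so 48, with a true difference of 0 (implied, not stated).
- With dropout: 48/0.80 = 60 per group, 120 in total.

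**What the limit permits.**
- Share of the historical effect that may be lost: 0.21/0.21 = 100%.
- Boundary for the experimental mean with control at 0.38: 0.38 - 0.21 = 0.17, the historical placebo mean.

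**How often a worse arm passes.** SE = 0.35 × √(2/48) = 0.0714. For a true deficit x, P(pass) = Φ((0.21 - x)/0.0714 - 1.96).

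| True deficit (mL/min) | Share of effect lost | P(pass) |
|---|---|---|
| 0.0525 | one quarter | 60% |
| 0.105 | one half | 31% |
| 0.15 | 71% | 13% |
| 0.19 | 90% | 5% |

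The largest observed deficit that still passes is 0.21 - 1.96 × 0.0714 = 0.070, one third of the historical effect.

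**Sensitivity to the SD (assumed values).** Entry is capped at 0.25 mL/min, so the SD could be below 0.35. For a true loss of half the effect, P(pass) is 54% at SD 0.25 (SE 0.0510) and 73% at SD 0.20 (SE 0.0408). Better precision makes it easier for a materially worse arm to pass.

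**Uncertainty of the historical effect.** Neither its confidence interval nor the group sizes are given.
- If p were exactly 0.001, then z = 3.29 and the lower 95% limit is 0.21 × (1 - 1.96/3.29) = 0.085. Because the protocol gives p < 0.001, this is a floor under a normal approximation.
- Assuming 80 to 200 per group with the stated SDs, the lower limit is 0.21 - 1.96 × √((0.48² + 0.13²)/n), which is 0.10 at n = 80 and 0.14 at n = 200.
- Suppose one of these were the true effect here. An arm equal to placebo would then have that deficit and would pass with probability Φ((0.21 - 0.085)/0.0714 - 1.96) = 42%, or 34% at 0.10 and 16% at 0.14.

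**The case against.** The choice is disclosed. The protocol states the source of the limit and gives the exploratory character of the trial as its reason, so a careful reader can see what -0.21 means. The sample-size arithmetic is correct. The plan already reports the 95% CI and makes the per-protocol set the main analysis. An arm that loses nearly all of the benefit would rarely pass: about 5% of the time at a true deficit of 0.19. All of this stands. It does not remove the point, because the exploratory reasoning is not carried into the decision rule, whose conclusion is unqualified.

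Some stronger readings are tempting, but the documents do not support them:
- A reader might infer that half-dose pilocarpine alone would fall within the limit and pass. Section 4.5 says only that it is less effective and gives no half-dose mean. A true deficit inside the limit is also not the same as passing.
- A reader might fault the limit for not showing what the herbal granule adds. That is mainly a consequence of a two-arm design without a half-dose-alone arm, and a tighter limit would not isolate the contribution either.
- A reader might infer that the protocol concedes a weaker effect in irradiated patients. Section 4.2.2 says that "its efficacy diminishes when a significant portion of the glands is damaged", but this refers to gland damage in either population, and 4.3.1.1 describes pilocarpine as proven effective after radiotherapy. What remains is that the estimate comes from a Sjögren's trial alone, while this trial enrols both groups.
- Equal efficacy is a goal in the design rationale of 4.5, not the conclusion that 13.3.1.2 would draw.

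**Conclusion.** The point holds. The limit equals 100% of one undiscounted point estimate. Meeting it shows that the deficit is smaller than the full historical pilocarpine effect, and no more. It does not support the unqualified conclusion in 13.3.1.2 and the synopsis, nor the equal-efficacy goal in 4.5.

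On the plan's own figures, an arm that truly loses half the effect would be called not inferior about three times in ten, and one that loses a quarter six times in ten. These rates assume SD 0.35, 48 evaluable per arm, a normal approximation and a two-sided 95% CI. The 42% for a placebo-like arm rests on two further assumptions: a historical p of exactly 0.001, and a true effect in this population equal to the resulting lower limit of 0.085. It illustrates the risk and is not an estimate of it. A reader might go further and posit a still smaller effect here, but the documents give no figure for such a shift between populations.

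**What to change.** In 13.3.1.2 and the synopsis, replace the conclusion attached to -0.21 with a statement that the deficit is smaller than the full 5 mg pilocarpine-versus-placebo difference of the cited trial. Do not claim non-inferior or equal efficacy on -0.21 alone, and bring the claims in 4.1 and 4.5 into line. Report the share of the historical effect that the CI limit retains: with lower limit L for experimental minus control, this is 1 + L/0.21.

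If the non-inferior label is to be kept, reserve it for a second step, tested only after the first succeeds and read from the same CI, against a retention margin that the sponsor chooses and justifies. State the power of that step at the present size. For illustration only, a limit of -0.105 (half the effect) has power Φ(0.105/0.0714 - 1.96) = 31% with truly equal arms and 48 per arm. For 90% power it would need 2 × 0.35² × (1.960 + 1.282)² / 0.105² = 234 evaluable per arm, or 586 in total after 20% dropout.

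The rewording needs no added participants, and the ordered step on one interval costs no alpha. The price is a more modest primary claim. In the illustration, truly equal arms would miss the non-inferior label about 69% of the time at the planned size.

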## 9. Trial design

### 9.1. Trial design

## Version 2.6

- This study is a prospective, randomized, open-label, parallel-group, multi-center, and controlled trial involving participants from four clinical research centers in Korea. Eligible participants will be randomly allocated to either the experimental or control group after screening based on the inclusion and exclusion criteria. The patients will receive treatment for 12 weeks. The unstimulated and stimulated salivary flow rate (SFR) test, visual analog scale (VAS), salivary scintigraphy, and questionnaires for oral symptoms and quality of life will be assessed for up to 12 weeks after the first visit.

**9.2. Trial schedule**

| Timepoint
Assessment           | Screening
Period | Treatment period |      |               |      |               |       |                |
|-----------------------------------|---------------------|------------------|------|---------------|------|---------------|-------|----------------|
|                                   | -1w - 0w            | 1w               | 2-3w | 4w            | 5-7w | 8w            | 9-11w | 12w            |
|                                   | V1
(-1w~0d)      | V2
(0w)       |      | V3
(4w±2d) |      | V4
(8w±2d) |       | V5
(12w±2d) |
| Informed consent                  | ●                   |                  |      |               |      |               |       |                |
| Demographics                      | ●                   |                  |      |               |      |               |       |                |
| Medical examination               | ●                   |                  |      |               |      |               |       |                |
| Physical examination              | ●                   | ●                |      | ●             |      | ●             |       | ●              |
| Vital signs                       | ●                   | ●                |      | ●             |      | ●             |       | ●              |
| Blood tests                       | ●                   |                  |      | ●             |      | ●             |       | ●              |
| 12 lead ECG                       | ●                   |                  |      |               |      |               |       |                |
| Random allocation                 | ●                   |                  |      |               |      |               |       |                |
| Pilocarpine          |                     | ●                | ●    | ●             | ●    | ●             | ●     | ●              |
| Baekhogainsa m-Tang  |                     | ●                | ●    | ●             | ●    | ●             | ●     | ●              |
| OHIP-14                           |                     | ●                |      | ●             |      | ●             |       | ●              |
| EQ-5D-5L                          |                     | ●                |      | ●             |      | ●             |       | ●              |
| VAS                               | ●                   |                  |      | ●             |      | ●             |       | ●              |
| Salivary flow test (SFR)          | ●                   |                  |      | ●             |      | ●             |       | ●              |
| Salivary scintigraphy             |                     | ●                |      |               |      |               |       | ●              |
| Monitoring adverse events         |                     | ●                |      | ●             |      | ●             |       | ●              |
| Evaluating concomitant medication |                     | ●                |      | ●             |      | ●             |       | ●              |

**9.3. Dosage and administration of the trial drugs**

Version 2.6

|                    |                                 | Dosage                                  | Administration                                              | periods  |
|--------------------|---------------------------------|-----------------------------------------|-------------------------------------------------------------|----------|
| Experimental group | Pilogen tab                     | half table (2.5 mg)
four times a day | Four times a day
(after each meal and
before bedtime) | 12 weeks |
|                    | Baekhogainsam-tang Ext. Granule | One packet (4 g)
three times a day   | Three times a day
(before each meal)                     | 12 weeks |
| Control group      | Pilogen tab                     | one tablet (5 mg)
four times a day   | Four times a day
(after each meal and
before bedtime) | 12 weeks |

#### 9.4. Combination therapy

- None

#### 9.5. Random allocation

#### 9.6. Methods of registration and randomization

- An independent statistician, blinded to the study design and purpose, will perform the random allocation of a total of 120 patients to the experimental group or the control group in a 1:1 ratio using a stratified block randomization method (a block size of 4).
- Random numbers will be generated by a computerized random-number generator using the block-randomization method of SAS version 9.1.3 (SAS Institute Inc., NC, Cary, USA) for sequence generation.

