## 5.3. Methods of management and storage of clinical trial drugs

- The clinical trial pharmacist is responsible for the acquisition, storage, preparation, management, and return of drugs used in clinical trials. The clinical trial pharmacist shall confirm in writing the receipts and quantity of clinical trial drugs received, sign them, and manage them appropriately.
- Clinical trial drugs are administered by the clinical trial pharmacist according to the principal investigator's prescription, and the clinical trial pharmacist must accurately record the

Version 2.6

clinical trial drugs and management given to each participant.

- This clinical trial is an open clinical trial, identified by the test subject identification number, and the clinical trial drug prescribed to each test subject and the returned clinical trial drug should be properly recorded.
- When the clinical trial is suspended or terminated, the clinical trial pharmacist must return the unused clinical trial drug to the clinical pharmacy of Kyung Hee University Medical Center and store the return certificate, and the clinical pharmacy of Kyung Hee University Medical Center must discard the returned clinical trial drug.

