## Version 2.6

- creatinine >1.5 times the upper limit of each hospital standard, or creatinine clearance  $\leq$  60 mL/min
- Patients taking following medications are also excluded: coumadin, heparin, warfarin, aspirin, anticholinergics, first-generation antihistamines, antidepressants with anticholinergic effects, monoamine oxidase inhibitors, diuretics, mineralocorticoids,  $\beta$ -adrenaline antagonist, or digitalis; patients taking low-dose aspirin or  $\beta$ -adrenaline antagonist can participate in the protocol based on the cardiologist's opinion.
- pregnancy or lactation, disagreement with proper contraception
- Failure to use appropriate contraception methods (male participants), participants who did not agree to contraception for 4 weeks after the end of administration of the trial drug (both male and female)
- galactose intolerance, Lapp lactase deficiency, or glucose-galactose malabsorption
- difficulty in oral administration of a clinical trial drug
- significant hypersensitivity to Baekhogainsam-Tang or components
- significant hypersensitivity to pilocarpine
- Participants who is deemed unsuitable for participation in clinical trials at the discretion of the investigator due to various reasons including screening test results
- cognitive disorder; inability to read and write

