**8.3. Sample size**

- 120 participants (Experimental group 60, control group 60)
- Sample size by clinical trial institution

|  |                                     |                                     |                  |                                           |       |
|--|-------------------------------------|-------------------------------------|------------------|-------------------------------------------|-------|
|  | Kyung Hee University Medical Center | Inha University College of Medicine | Myongji Hospital | Kyung Hee University Hospital at Gangdong | Total |
|--|-------------------------------------|-------------------------------------|------------------|-------------------------------------------|-------|

Version 2.6

|                    |    |    |   |    |     |
|--------------------|----|----|---|----|-----|
| Experimental group | 32 | 16 | 2 | 10 | 60  |
| Control group      | 32 | 16 | 2 | 10 | 60  |
| Total              | 64 | 32 | 4 | 20 | 120 |

- Competitive recruitment
- Sample size in Kyung Hee University Medical Center: 64 (experimental 32, control 32)

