#### 9.7. Managements of random allocation

- When a random assignment table is prepared, it is managed by an independent statistician.
- When the test subjects listen to the explanation of the study and write a consent form for participation in the clinical trial, they are given screening numbers in order.
- Participants who pass the screening test during their first visit will be assigned a registration number and group based on the random assignment table stored by an independent statistician.

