## 9.8. Test subject number

- A screening number is assigned to the test subjects who have agreed to participate in the clinical trial in the order of time of written informed consent. The screening number starts with KH-S001, and the rest, excluding KH-, consists of four digits in total and three numbers (Kyung Hee University Medical Center 'KH-', Inha University Hospital 'IH-', Myongji Hospital 'MJ-', and Kyung Hee University Hospital at Gangdong 'KD-'). Finally, test subject number (registration number) is assigned in order of the data the screening passes were determined (in the order of the time of informed consent if the same date) and assigned to the group according to a pre-written random assignment table. The test subject identification number starts with each KH-R1001, and the rest, excluding KH-, consists of five digits and four numbers (Kyung Hee University Medical Center 'KH-', Inha University Hospital 'IH-', Myongji Hospital 'MJ-', and Kyung Hee University Hospital at Gangdong 'KD-'). The identification number shall be assigned as follows. One (or two) of the first number is assigned to the group, and the last three numbers are assigned in the order of random assignments. The screening number and test subject identification number assigned to each test subject are used as codes to recognize the test subject until the end of the clinical trial.

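### A fixed block size of 4, printed in an open-label protocol, makes up to one third of allocations deducible in advance if blocks run within site

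*Protocol*

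**What the plan says.** Section 9.6 has an independent statistician allocate 120 patients "to the experimental group or the control group in a 1:1 ratio", "using a stratified block randomization method (a block size of 4"). It gives one block size and does not name the stratification factor. No varying or undisclosed size appears elsewhere in the protocol.

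Section 5.3 states: "This clinical trial is an open clinical trial". Under section 9.8 the subject number itself shows the arm ("One (or two) of the first number is assigned to the group"), its last three digits follow the order of randomisation, and it carries a site prefix. The regimens also differ visibly (section 9.3).

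Section 9.7 assigns a patient who passes screening to a "group based on the random assignment table stored by an independent statistician". Section 8.3 sets site totals of 64, 32, 4 and 20, each split equally by arm, for example "Sample size in Kyung Hee University Medical Center: 64 (experimental 32, control 32"). Section 8.2 lets a candidate be excluded if "deemed unsuitable for participation in clinical trials at the discretion of the investigator".

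The primary comparison (section 13.3.1.2) is the week-12 difference in mean unstimulated salivary flow rate (SFR) with a 95% confidence interval. Covariate adjustment is added only if baseline values differ significantly.

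**The concern.** Keeping the list with an independent statistician protects it from being read. It does not protect it from being inferred. When block size is fixed and known and past allocations are visible, the tail of each block follows by subtraction. A recruiter who knows or strongly suspects the next arm can delay or hasten a consent, or use the discretionary exclusion, according to how well the candidate is expected to do. The arms could then differ in prognosis at entry. In a non-inferiority trial, such a difference could push the result in either direction. An unadjusted week-12 comparison would carry it straight into the estimate.

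**Working it through.** **The plan's own figures.** The protocol gives no figure for predictability. Its sample size reproduces: 2 × 0.35² × (1.645 + 1.282)² / 0.21² = 47.6, so 48 per arm, and 48 / 0.8 = 60 per arm. This does not bear on the point except for the standard error used below.

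**Inputs.** Block size 4 and ratio 1:1 (section 9.6); open allocation (5.3); site totals 64, 32, 4 and 20 (8.3); SD 0.35 and margin 0.21 mL/min (8.4).

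**Certain allocations.** A block holds two patients per arm (A, B), so there are 6 equally likely orderings and 24 positions.
- AABB and BBAA: the 3rd and 4th are certain, 2 × 2 = 4.
- The other four orderings: only the 4th is certain, 4 × 1 = 4.
- Share certain: 8/24 = 1/3.

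**Best guess.** Always guess the arm with more places left and toss a coin at ties. Hit rates by position are 1/2, 2/3, 2/3 (certain in 1/3 of blocks, a tie in 2/3: 1/3 + 2/3 × 1/2) and 1. The mean is 17/24 = 70.8%, against 50% with simple randomisation.

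**Per site, if site is the stratum.** The totals are 16, 8, 1 and 5 whole blocks. Expected certain allocations are 64/3 = 21.3, 32/3 = 10.7, 4/3 = 1.3 and 20/3 = 6.7, together 120/3 = 40.

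**Other stratifications.** If blocks are nested in site by two aetiology groups (assumed split 50/50, staff know the stratum), simulation gives 32%, 31%, 29% and 8% at the sites of 64, 32, 20 and 4. If blocks run across sites, no site need see a whole block and the share is lower.

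**Possible bias.** Let δ be the difference in SFR between patients steered to one arm and to the other (assumed; the protocol gives no value). If every certain allocation is used, bias = δ/3.

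| δ (mL/min) | Bias | Share of 0.21 margin |
|---|---|---|
| 0.02 | 0.007 | 3% |
| 0.05 | 0.017 | 8% |
| 0.10 | 0.033 | 16% |

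With 48 per arm the standard error is 0.35 × √(2/48) = 0.071, so 0.017 is about 0.23 standard errors.

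**Comparators.** The observer knows the set of sizes but not their order. Mixed sizes were simulated for strata of 20 to 64 patients.

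| Blocks | Certain | Best-guess hit rate |
|---|---|---|
| Fixed 4 | 33.3% | 70.8% |
| Fixed 6 | 25.0% | 68.3% |
| Fixed 8 | 20.0% | 66.6% |
| Mixed 4, 6 | about 6% | about 69% |
| Mixed 4, 6, 8 | about 2% | about 67-68% |

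**The case against.** A reader might infer that sites simply know one third of upcoming allocations. The protocol does not support that without a condition. Section 9.6 says the blocks are stratified but not by what, and that detail may properly sit in another document. Equal per-arm quotas that are all multiples of 4, together with site-prefixed numbers, make site likely but do not establish it. Recruitment is competitive, so a site may also stop mid-block.

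A reader might also infer that the trial is biased or its conclusion unsafe. Nothing shows that anyone used the information. Numbers are issued in the order screening is passed, with ties broken by consent time (9.8), and the group is assigned only afterwards (9.7). This limits re-ordering of patients already screened and leaves mainly consent timing and discretionary exclusion. Numerical entry limits on SFR and dry-mouth score (8.1) restrict how far baseline can be selected. Monitors check concealment of the random numbers (16.5). The illustrative bias is small against the margin, has no fixed direction, and assumes every certain allocation is exploited.

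These points limit the size and certainty of the problem but do not remove it. None of the safeguards stops deduction from open past allocations. Adjustment triggered by a significant baseline difference would seldom respond to a modest shift, and it cannot remove selection on unmeasured prognosis.

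It is also fair to say that varying the block size leaves the best guess almost as good. The gain lies in removing certainty.

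**Conclusion.** The point stands as a conditional weakness in allocation concealment that is cheap to reduce. If blocks run within site and staff track their own allocations, up to one third of allocations (about 40 of 120) can be deduced with certainty before enrolment, and the best-guess hit rate is 70.8%. If blocks run across sites, the share is lower. The arithmetic is exact for completed blocks of 4; the within-site condition is an inference from the quotas and numbering. The resulting bias cannot be sized from the protocol: 0.017 mL/min rests on an assumed δ of 0.05 and full exploitation. The finding does not show that selection occurred or that the non-inferiority conclusion would change.

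**What to change.** For any allocations not yet made, generate the list with randomly varying block sizes, for example 4 and 6, or 4, 6 and 8. Keep the sizes in a restricted randomisation file, and delete the block size in section 9.6 from the protocol that sites hold.

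The cost is regenerating the unused part of the list. Exact balance between arms within each site is then no longer guaranteed, so the equal per-arm quotas in the summary and section 8.3 should be stated as approximate. This matters most at the 4-patient site, where a block of 6 or 8 would never complete. No endpoint, sample size or treatment changes.

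How many patients the change would reach is unknown: version 2.6 is dated November 2023, three years after version 1.0, and section 6 allows four years from ethics approval. If enrolment is complete, report the predictability as a limitation.
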